#### Multiple imputation

If any outcomes are randomly missing, multiple imputation will be used to enhance statistical power. Assuming that the missing data follow the Missing at Random assumption, the analysis results from multiple imputed datasets will be combined using Rubin's Rules. Methods such as comparison of distribution similarity, regression results, and Monte Carlo error assessment will be used to ensure the quality of imputation.

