### Outcomes

Participants who take the granules for more than 80% of the expected duration will undergo the following assessments before and after the 12-week treatment.

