#### Outcome analysis

All data will be analyzed using SPSS 26.0 after unblinding. Continuous outcomes will be initially assessed for distributional characteristics by Shapiro-Wilk test. For approximately normally distributed outcomes, *t*-tests or ANCOVA will be applied to compare groups; for variables with marked deviation from normality, nonparametric alternatives such as the Mann–Whitney *U*-test and Wilcoxon signed-rank test will be considered. The categorical variables will be analyzed using the χ^2^ test.

Baseline covariates and other prognostic factors will be incorporated into ANCOVA models to improve estimation precision and control for residual confounding. Repeated measurements or longitudinal data will be analyzed using linear mixed-effects models, allowing for appropriate modeling of within-subject correlations, and evaluation of treatment-by-time interactions. The hierarchical testing procedure will be used to adjust multiple secondary outcomes. Sensitivity analysis will be conducted to reduce the impact of protocol deviations.

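### Multiple imputation is justified by a power gain it will hardly deliver, does not fit the rank and chi-square tests as written, and competes with a last-observed-value rule for the full analysis set

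*Protocol article*

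**What the plan says.** Four places in the protocol article bear on this point.

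- **Multiple imputation.** "If any outcomes are randomly missing, multiple imputation will be used to enhance statistical power". Missing at random is assumed, and "the analysis results from multiple imputed datasets will be combined using Rubin's Rules". The rule covers any outcome.
- **Outcomes.** "Participants who take the granules for more than 80% of the expected duration will undergo the following assessments", and these take place "before and after the 12-week treatment". The text therefore gives one post-baseline assessment. The schedule in Table 1 is not shown.
- **Outcome analysis.** "For approximately normally distributed outcomes, *t*-tests or ANCOVA will be applied to compare groups". Where an outcome is clearly non-normal, rank tests (Mann-Whitney, Wilcoxon signed-rank) are to be considered. Categorical variables get a chi-square test. ANCOVA models are to include baseline covariates and other prognostic factors.
- **Analysis sets.** The full analysis set holds everyone randomised and takes the last observed data as the outcome. The per-protocol set, which requires compliance and completed case report forms, serves the primary efficacy analysis.

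**The concern.** Three statements do not fit together.

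1. Power is the wrong reason for imputing. Imputation is there to estimate the effect in all randomised participants under a stated assumption and to carry the uncertainty from missing data into the standard error. Someone who misses week 12 has only baseline data to impute from, and the ANCOVA already uses those data.
2. Rubin's Rules combine an estimate with its standard error. A rank or chi-square test returns a statistic and a p-value. For a markedly skewed or categorical outcome, the testing rule and the pooling rule do not connect as written.
3. If the last observed value is used in the full analysis set, no outcome is missing there for anyone with a baseline value, and the imputation rule has nothing to act on.

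At stake is which missing-data rule produces the intention-to-treat result, and whether skewed outcomes such as cytokines and triglycerides get an efficient analysis that can be pooled. That these will be skewed is an expectation; the document does not say so.

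**Working it through.** **The plan's own figure.** The imputation section gives no number, so the check starts from Sample size: means 1600 and 1440 cm/s, SDs 260 and 234, two-sided alpha 0.05, power 0.90. For an unequal-variance t-test (noncentral t), power is 0.899 at 51 per group and 0.904 at 52. The stated 52 is reproduced.

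**Why matching covariates give no gain.** A participant with covariates but no outcome carries no information about the regression of outcome on covariates. Imputing from that same regression returns the complete-case estimate plus simulation noise.

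**When some gain is possible.** For an unadjusted t-test with baseline in the imputation model, the variance of the difference shrinks by about 1 − ρ²f, where f is the missing fraction and ρ the baseline correlation. Take ρ = 0.7, f = 0.15, SD 247 (the mean of 260 and 234), 60 × 0.85 = 51 observed per arm, and a difference of 100 cm/s (the stated minimal important difference):

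- Complete cases: SE = 247 × √(2/51) = 48.9; 100/48.9 = 2.04; power ≈ Φ(2.04 − 1.96) ≈ 0.53.
- With imputation: SE = 48.9 × √(1 − 0.49 × 0.15) = 47.1; 100/47.1 = 2.12; power ≈ 0.57.

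**Simulation.** 60 per arm, SD 247, about 15% missing depending on baseline, 20 imputations, 1,500 runs per scenario; Monte Carlo error about 0.01. The correlations are assumptions, because the document gives none.

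| Analysis | Baseline correlation, difference (cm/s) | Complete case | Imputed |
|---|---|---|---|
| ANCOVA, same covariate in both models | 0, 160 | 0.896 | 0.886 |
| | 0.5, 160 | 0.959 | 0.955 |
| | 0.7, 100 | 0.787 | 0.787 |
| t-test, baseline in imputation model | 0, 160 | 0.901 | 0.889 |
| | 0.5, 160 | 0.905 | 0.913 |
| | 0.7, 100 | 0.534 | 0.563 |
| ANCOVA, week-12 auxiliary in imputation model (residual correlation 0.5) | 0.7, 100 | 0.787 | 0.804 |
| Same, residual correlation 0.8 | 0.7, 100 | 0.808 | 0.843 |
| Mann-Whitney effect P(X<Y), pooled | 0.5, 160 | 0.902 | 0.906 |
| | 0.7, 100 | 0.512 | 0.552 |

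With no treatment effect, the pooled P(X<Y) rejected in 0.055 of runs.

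**Rank test against log-scale ANCOVA.** Assume a log-normal outcome, a difference of 0.5 SD on the log scale and 51 per arm. For ANCOVA adjusted for the log baseline, power ≈ Φ(0.5 × √(51/2)/√(1 − ρ²) − 1.96). For Mann-Whitney, the factor 1/√(1 − ρ²) is replaced by √(3/π).

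| Assumed ρ | Log ANCOVA, formula | Log ANCOVA, simulated | Mann-Whitney, formula | Mann-Whitney, simulated |
|---|---|---|---|---|
| 0 | Φ(2.525 − 1.96) = 0.71 | 0.71 | Φ(2.467 − 1.96) = 0.69 | 0.68 |
| 0.5 | Φ(2.915 − 1.96) = 0.83 | 0.81 | 0.69 | 0.68 |
| 0.7 | Φ(3.536 − 1.96) = 0.94 | 0.94 | 0.69 | 0.69 |

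The gain comes from adjusting for baseline, not from imputing.

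**Last observed value against imputation.** With one post-baseline visit, a drop-out's last observed value is the baseline value, which randomisation makes equal in expectation between arms. If drop-out is equal in both arms and unrelated to baseline, the expected difference of 160 becomes 0.90 × 160 = 144 at 10% drop-out and 0.85 × 160 = 136 at 15%. Imputation under missing at random targets 160. The two rules give different answers.

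**The case against.** The strongest reply is that little here is impossible. Imputation can add power: the protocol allows a t-test and does not confine the imputation model to the ANCOVA covariates, and if only one measurement is missing, other week-12 data can help. That stands, and it is why the point is limited to matching covariates. The gain is 1 to 4 percentage points where it exists, and someone who misses the whole visit supplies no week-12 auxiliary data.

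A reader might also infer that rank-tested outcomes leave nothing to pool. The document does not support that. It speaks of combining analysis results without saying which, rank tests are only to be considered, and P(X<Y) or a risk difference can be pooled. The narrower statement remains: the tests as named do not supply what Rubin's Rules need.

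A reader might further infer that every drop-out falls out of each rank comparison. The last-observed-value rule contradicts this for the full analysis set, because anyone with a baseline value stays in.

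It is fair to say that an article may leave imputation variables and pooled quantities to a fuller document. The stated purpose and the two competing missing-data rules are in this text, however, and are not omissions. Finally, the single post-baseline visit rests on the Outcomes section; Table 1 is not shown, and mixed models are mentioned for repeated measurements.

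**Conclusion.** The point holds in limited form. With assessments at baseline and 12 weeks, imputing from the ANCOVA's own covariates changes power by 0 to −1 point. A gain of about 1 to 4 points needs information that the analysis model lacks. The rank and chi-square tests do not connect to Rubin's Rules as written, and the last-observed-value rule leaves the full analysis set with nothing to impute.

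Deleting the power clause alone would change no result. What would change results is a single missing-data rule and a baseline-adjusted log-scale analysis: power about 0.81 against 0.68 for Mann-Whitney at an assumed correlation of 0.5, and about 0.71 against 0.68 at zero correlation. These figures rest on log-normal data and the assumed correlations.

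None of this shows that the trial is underpowered or that its type I error is inflated. UACR is not among the efficacy outcomes affected, because the protocol lists it under safety.

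**What to change.** 1. For skewed continuous efficacy outcomes such as cytokines and triglycerides, use ANCOVA on the log scale adjusted for the log baseline value, report a ratio of geometric means, and pool by Rubin's Rules. Keep the rank test as a sensitivity check. For categorical outcomes, pool a risk difference or a logistic-regression estimate.
2. Reconcile Analysis sets with Multiple imputation: in the full analysis set, use multiple imputation instead of the last observed value.
3. Replace the power rationale with the purpose of estimating the effect in all randomised participants under missing at random.

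The cost is a change of wording before unblinding and a few more model runs. The downside is that results for skewed outcomes are read as ratios instead of differences in the original units.

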### Conditions for suspension, drop-out and termination

In accordance with medical standards, participant safety considerations, and GCP requirements, investigators will determine whether a participant needs to suspend or drop-out. Participants will be classified as drop-out if they are newly diagnosed with other diseases that may influence the trial, if they begin using other traditional Chinese medicines with similar therapeutic effects, or if they are lost to follow-up during the observation period.

An adverse event refers to any unfavorable medical occurrence during the study, regardless of whether it is causally related to the intervention. It includes clinically significant abnormalities in electrocardiogram, liver function, or renal function tests, as well as any subjective symptoms of discomfort reported by the participants. If it occurs, investigators should record, assess the severity and the relationship with the trial, and observe until returning to normal. A serious adverse event is any unfavorable medical occurrence that result in hospitalization, disability, incapacity, or even life-threatening conditions. It requires immediate medical management plus immediate reporting to the principal investigator once known, followed by expedited reporting to the ethics committee. If more than half of the participants experience serious adverse events, the trial must be terminated.

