### Sample size

The mean ± SD of baPWV among T2DM patients was 1548.87 ± 305.48 cm/s in Beijing, China (aged 20–80 years) (21), 1580 ± 324 cm/s in Nanchang, China (aged 17–75 years) (22), and 1534.2 ± 254 cm/s in Kagoshima, Japan (aged 22–84 years) (23). Among healthy people, it was 1200 ± 150 cm/s (aged 40–49 years), 1390 ± 190 cm/s (aged 50–59 years), 1630 ± 300 cm/s (aged > 60 years) in Xinjiang, China (24).

Considering that the above data were derived from small-sample studies and the age ranges were not consistent with this study, we hypothesized that the baPWV was 1600 ± 260 cm/s for T2DM patients aged 40–85 years, and YQYYHX was expected to reduce it to 1440 ± 234 cm/s (25, 26). A change of 100 cm/s may represent a minimal clinically important difference (27). This study is designed by superiority, and the ratio between the treatment and control groups is 1:1. With a two-sided α = 0.05 and β = 0.1, the sample size is calculated to be 52 in each group using a *t*-test allowing unequal variances in PASS 15. The formula is as follows.

$$\begin{array}{l} n=\frac{{\left(Z_{1-\alpha /2}\;+\;Z_{1-\beta }\right)}^{2}\cdot 2\sigma^{2}}{{\left(\mu_{1}-\mu_{2}\right)}^{2}} \end{array}$$

Considering a 10%−15% dropout rate, 60 patients are needed in each group and the total sample size is 120.

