### Intervention

Basic treatments include metformin, acarbose, insulin, statins, evolocumab, and other standard medical therapies. It is not fixed, individualized plans will be developed by the attending clinicians before the trial, to maintain HbA1c below 8.0% (28) and LDL-C below 1.4 mmol/L (29). Basic treatments will remain unchanged and other TCM therapies are prohibited during the trial.

Participants will take YQYYHX granules or placebo granules for 12 weeks. They should take it 30 min before meals or other medication, at a dose of 12 g per administration, twice daily. The placebo granules contain 10% inert ingredient and 90% excipient (dextrin), with a similar shape, color, and odor as YQYYHX granules.

YQYYHX granules from three different batches were analyzed by Ultra-performance Liquid Chromatography – Mass Spectrometry (Figure 2). Methanol (the extraction solvent) was used as the blank control. The raw data were processed using Progenesis QI 2.4 and subsequently analyzed using a self-built TCM database 2.0 developed by Beijing Junfei Technology Co., Ltd. The top 20 compounds with the largest peak area are shown in Table 2, such as daidzin, salvianolic acid L, and oleamide.

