#### Primary outcome

Brachial–ankle pulse wave velocity (baPWV).

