### Statistical plan

#### Analysis sets

The full analysis set (FAS) includes all participants who were randomized, using their last observed data as the trial outcome for intention-to-treat analysis. The per-protocol set (PPS) refers to participants who strictly adhered to the trial protocol, demonstrated good compliance, did not take prohibited medications during the trial, and completed the required case report forms. It will be utilized for the primary efficacy analysis. The safety set (SS) comprises all participants who were randomized, received at least one dose of the study treatment, and have post-treatment safety data available. Statistical descriptions and analyses of their safety outcomes and adverse event incidence will be performed.

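### The drop-out rule puts a new diagnosis and use of similar Chinese medicines in one class with loss to follow-up, and the article does not secure week-12 baPWV for participants who could still be measured

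*Protocol article*

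**What the plan says.** The section on suspension, drop-out and termination leaves the decision to the investigator: "investigators will determine whether a participant needs to suspend or drop-out". It then lists three grounds under one label. The first is "Participants will be classified as drop-out if they are newly diagnosed with other diseases that may influence the trial". The other two follow: "if they begin using other traditional Chinese medicines with similar therapeutic effects, or if they are lost to follow-up during the observation period".

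Four other sections bear on what the label means in practice:

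- **Intervention:** "Basic treatments will remain unchanged and other TCM therapies are prohibited during the trial". This covers all other Chinese medicine, whereas the drop-out ground covers only products with similar effects.
- **Sample size:** "Considering a 10%−15% dropout rate, 60 patients are needed in each group".
- **Outcomes:** "Participants who take the granules for more than 80% of the expected duration will undergo the following assessments before and after the 12-week treatment".
- **Analysis sets:** "The full analysis set (FAS) includes all participants who were randomized", with the last value observed standing as the outcome. The per-protocol set excludes anyone who took prohibited medication, and it is the set named for the primary efficacy analysis.

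**The concern.** The three grounds differ in kind. A participant lost to follow-up cannot be measured. A participant with a new diagnosis, or one who has started another herbal product, usually can be. Giving all three the same status invites the site to treat obtainable outcomes as missing.

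The first two grounds arise after randomisation and may depend on treatment. A new diagnosis could be a harm of the granules, or the vascular progression that the trial hopes to prevent. Turning to another Chinese medicine could follow from limb symptoms that have not improved, which would be more likely on placebo if the granules work. If such participants are replaced by an earlier value or left out, the comparison is no longer between the groups as randomised.

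**Working it through.** **1. Can the outcome be obtained, and what does the plan do with it?**

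| Ground for drop-out | Week-12 baPWV obtainable? | Treatment under the article |
|---|---|---|
| Lost to follow-up | No | Last value observed in the full analysis set |
| New diagnosis | Usually yes | Labelled drop-out; assessed under Outcomes if intake exceeds 80%; otherwise no stated route to a week-12 value |
| Similar Chinese medicine started | Usually yes | As above, and excluded from the per-protocol set as a user of prohibited medication |

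The Outcomes section places assessments only before and after treatment. For someone who leaves early, the last value observed is therefore the baseline value. The article also plans multiple imputation under a missing-at-random assumption. Either way, a substitute stands in for a measurement that could have been taken.

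**2. The plan's own sample size.** Inputs from the Sample size section: means 1600 and 1440 cm/s (difference 160), SDs 260 and 234, two-sided alpha 0.05, power 90%. For the unequal-variance t-test, power is 0.899 at 51 per arm and 0.904 at 52, so the stated 52 reproduces. Inflation: 52/(1 − 0.10) = 57.8, rounded up to 58, and 52/(1 − 0.15) = 61.2, rounded up to 62. The stated 60 corresponds to 1 − 52/60 = 13.3%, inside the stated range. The sample size is not in error on this account. It does show that drop-out is handled as a loss to be offset: 10% to 15% of 60 is 6 to 9 participants per arm.

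**3. Illustrative bias in a completer contrast.** Let p be the proportion of an arm dropped under the first two grounds. Let D be how much higher (worse) their true week-12 mean is than that of the others in the arm. The full-arm mean equals the completer mean plus p × D, so leaving drop-outs out lowers the arm's mean by p × D. The contrast shifts by (p1 − p2) × D. Neither p nor D is in the documents. I assume D = 100 to 200 cm/s; 100 is the protocol's own minimal important difference.

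- 15% against 5%: 0.10 × 100 = 10 and 0.10 × 200 = 20 cm/s.
- 10% against 5%: 0.05 × 100 = 5 and 0.05 × 200 = 10 cm/s.
- Equal rates and equal D: 0.

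The range is 5 to 20 cm/s, or 5/160 = 3% to 20/160 = 12.5% of the planned difference. If more are dropped on the granules, benefit is overstated; if more are dropped on placebo, it is understated.

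**4. Scale.** The standard error of the difference is √((260² + 234²)/n) = √(122,356/n), which is 45 cm/s at 60 per arm and 49 at 51. The assumed shift is thus about 0.1 to 0.4 standard errors.

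**The case against.** The strongest reply is that the loss of data is inferred. A reader might conclude that the rule cancels the week-12 visit, but the section assigns a label and says no such thing. A participant who took every dose to week 10 has 10/12 = 83% intake and so qualifies for assessment under Outcomes. This stands, and it is why the point concerns unreconciled sections and an unsecured measurement, not proven loss.

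Three further strong readings do not hold:

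- **Adverse events after drop-out go unrecorded.** The same section requires adverse events during the study to be recorded and followed until they return to normal.
- **The Intervention and drop-out sections contradict each other on Chinese medicine.** A general prohibition with drop-out reserved for similar products can be read as a graded consequence. One reconciled definition is still needed.
- **The fix recovers power from 0.899 (51 per arm) to 0.940 (60 per arm).** Both figures are correct, but the comparison charges the whole 15% allowance to these two grounds. Genuine loss to follow-up would remain.

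It is also fair to say that investigators are blinded, which limits arm-dependent discretion. Blinding does not stop the events themselves from differing by arm. Nor need someone who adds a similar product do worse at week 12, so D could be small. Finally, the full protocol may provide for follow-up after drop-out. But the article states the classification itself as a rule, and that rule can be judged as it stands.

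**Conclusion.** The point holds in limited form. The article classes two kinds of measurable participant with those lost to follow-up, on grounds that arise after randomisation, involve judgement and may depend on treatment. Apart from the 80% intake rule, nothing keeps them in follow-up. The analysis rules then replace or exclude them.

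Bias in either direction is possible, but its size cannot be derived from the documents. The 5 to 20 cm/s illustration rests on assumed rates and outcomes and describes a completer contrast. Under the last-value rule the shift would depend instead on how far drop-outs' true week-12 values lie from the values carried forward. This is a moderate weakness that should be corrected; it does not invalidate the trial or its sample size.

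**What to change.** In the drop-out section, separate stopping the granules, and intercurrent events (a new diagnosis, other Chinese medicine use), from withdrawal from the study. Limit drop-out to withdrawal of consent, death or loss to follow-up. All other randomised participants attend the scheduled week-12 baPWV, secondary and safety assessments. Their observed values are analysed in the randomised arm in the full analysis set. This is no comment on whether granules should be stopped in any participant.

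The change works only if two other sections follow it. Outcomes should not make assessment depend on intake, and Analysis sets should use the observed values, with the per-protocol set as supplementary. Record all other Chinese medicine use with dates, under one definition reconciled with the Intervention section.

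The cost is a short amendment and a small addition to the case report form, since the week-12 visit already exists. The estimate will include participants with other Chinese medicine use or new disease and may be slightly smaller than an on-treatment effect. The amendment would also come mid-trial: by March 10, 2026, 72 participants were enrolled and 38 had completed, so outcomes for up to 120 − 38 = 82 could still be affected. Document the amendment date, and retrieve any available week-12 data for earlier drop-outs where possible, so that the two follow-up regimes can be told apart.

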**Methods:**

This is a single-center, randomized, double-blind, placebo-controlled, parallel-group clinical trial. It will enroll 120 participants with T2DM and EVA, who will be randomized in a 1:1 allocation ratio to two groups. In addition to standard therapy, the treatment group will receive the YQYYHX granules, while the control group will receive a matched placebo. Based on mass spectrometry analysis, daidzin, salvianolic acid L, and oleamide were identified as the compounds with the largest peak area in YQYYHX. After a 12-week intervention, brachial-ankle pulse wave velocity (baPWV) is planned to be assessed as the primary outcome. Secondary outcomes are expected to include the ankle-brachial index, blood glucose levels, lipid profiles, inflammatory cytokines, 6-min walk test and questionnaires. Safety will be evaluated using liver transaminases, serum creatinine, and related indicators. Serum and fecal samples will be collected before and after treatment. The serum will be used for metabolomic and proteomic sequencing analysis, and feces will be used for metagenomic sequencing. Electronic case report forms are generated within the clinical record system, ensuring that all follow-up information is traceable. Subsequently, the data will be entered into a specific electronic data capture, and the data administrator will verify it.

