### Randomization, allocation and blinding

The clinical research methodology team generated a simple randomization list using the block-randomized method with SAS 9.4, applying the allocation ratio of 1:1. Blinding of the investigational drugs was performed by statisticians and independent third-party personnel not involved in the trial.

Participants are assigned random numbers and corresponding drug codes sequentially according to their enrollment order. The blinding codes are stored confidentially in sealed envelopes until the end of the trial. Both the investigators and participants are blind to treatment allocation. If a serious adverse event happens, the principal investigator will request an emergency unblinding envelope from the Good Clinical Practice (GCP) office.

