#### Interim analysis

A group sequential design will be adopted for statistical inference, with a prespecified interim analysis to be conducted when approximately 50% of the total information for the primary endpoint has accrued. Interim analysis results and unblinded data will be accessible only to the independent Data Monitoring Committee, which will mainly consist of statisticians, clinical and ethics experts.

An O'Brien-Fleming efficacy boundary will be applied to control the overall two-sided type I error rate at 0.05, using the Lan-DeMets alpha-spending function as an approximation. Statistical significance will be determined on the basis of the prespecified nominal significance level corresponding to each analysis. If the baPWV crosses the prespecified efficacy boundary at an interim analysis, early termination of the trial may be recommended.

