### Quality control

This trial is conducted in accordance with standard operating procedures for clinical trial management. All investigators have been authorized by the principal investigator, and have undergone appropriate training. A Trial Steering Committee is established to provide overall supervision of this study, and includes the principal investigator, as well as independent clinical and methodological experts. All granules are stored, managed, dispensed, and retrieved by professional pharmacists.

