### Trial status

Until March 10, 2026, 72 participants have been enrolled, and 38 have completed the observation period.

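### The mandatory safety stop pools both arms at more than 50% with a serious adverse event, so a large excess of harm on YQYYHX would not trigger it

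*Protocol article*

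**What the plan says.** The Protocol article, under *Conditions for suspension, drop-out and termination*, states: "If more than half of the participants experience serious adverse events, the trial must be terminated". No other numeric condition for stopping the whole trial on safety grounds appears in the article. The sentence names no arm, no comparison between arms, no relation to treatment, and no denominator (planned, enrolled or treated participants). The same section defines the event without regard to cause: "A serious adverse event is any unfavorable medical occurrence that result in hospitalization, disability, incapacity, or even life-threatening conditions".

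The surrounding design is as follows.

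- *Sample size*: "60 patients are needed in each group and the total sample size is 120", with 1:1 allocation.
- *Randomization, allocation and blinding*: "Both the investigators and participants are blind to treatment allocation".
- *Interim analysis*: "Interim analysis results and unblinded data will be accessible only to the independent Data Monitoring Committee". The only stopping criterion described there is the efficacy boundary on baPWV.
- *Quality control*: "A Trial Steering Committee is established to provide overall supervision of this study".
- *Trial status*, at 10 March 2026: "72 participants have been enrolled, and 38 have completed the observation period".

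**The concern.** A mandatory safety stop should be reachable when the study product causes a clear excess of serious harm. This one depends on the overall number of participants with an SAE. The plain reading of the sentence counts both arms together, and blinded investigators could not count in any other way. Half of the denominator is then on placebo and dilutes any signal from the herbal product.

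The difference between arms, which is the evidence of harm from the product, does not enter the rule. If the rule cannot be met under a large by-arm excess, the obligation to stop is empty. As far as the article shows, stopping for harm then rests on the discretion of the committees. As the only published figure, it may also suggest that SAE rates well below one half are acceptable.

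**Working it through.** **Inputs from the article.** 120 participants, 60 per arm, 1:1; 72 enrolled so far (36 per arm assumed); threshold more than one half.

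**Assumed inputs.** The article gives no SAE risks. Placebo is taken as 2%, 5% or 10%, and YQYYHX over a wide range.

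**1. The denominator.** The planned size was reproduced first. With SDs of 260 and 234 cm/s and a difference of 1600 − 1440 = 160 cm/s, the unequal-variance t-test has 89.9% power at 51 per arm and 90.4% at 52, so the stated 52 is right. Dividing by 0.90 and by 0.85 gives 58 and 62, which bracket the stated 60 per arm.

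**2. The count needed.** More than half of N participants is floor(N/2) + 1.

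| N | Participants with an SAE needed |
|---|---|
| 120 (planned) | 61 |
| 72 (enrolled) | 37 |
| 60 (half the planned number) | 31 |

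**3. The extreme case, with no assumed rate.** At 60 per arm, an SAE in every YQYYHX participant and in no placebo participant gives 60 + 0 = 60, exactly half, and the rule is not met. At 36 per arm, 36 + 0 = 36 of 72 also fails. In general, with n per arm the rule needs X_T + X_C > n. The number of placebo participants with an SAE must therefore exceed the number of YQYYHX participants without one.

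**4. Chance of meeting the rule at the final count.** P(X_T + X_C ≥ 61), with X_T ~ Bin(60, p_T) and X_C ~ Bin(60, p_C), computed exactly by convolution at p_C = 5%:

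| p_T | P(at least 61 of 120) |
|---|---|
| 30% | 1.3e-19 |
| 50% | 6.1e-11 |
| 60% | 7.3e-8 |
| 75% | 0.0003 |
| 80% | 0.0027 |
| 90% | 0.11 |
| 95% | 0.41 |

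For an even chance of meeting the rule, the YQYYHX risk must be about 99%, 96% or 91% when the placebo risk is 2%, 5% or 10%. A rough check: the expected count 60(p_T + p_C) must reach about 60.5, so at p_C = 5%, p_T ≈ 60.5/60 − 0.05 = 0.958.

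**5. The other reading, a running count of participants enrolled to date.** 100,000 simulated trials, permuted blocks of 4 (an assumption), SAEs counted at enrolment, the rule checked after each participant:

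| p_T against p_C | Checked from n = 10 | Checked from n = 20 |
|---|---|---|
| 80% against 5% | 39.7% | 24.9% |
| 60% against 5% | 9.4% | 2.5% |
| 30% against 5% | 0.38% | 0.014% |

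Blocks of 6, checked from n = 10, give 41.2%, 9.5% and 0.41%. On this reading, 100% against 0% always meets the rule at some point, because an incomplete block can leave the arms briefly unequal.

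**6. A by-arm comparison, for scale.** Fisher's exact test, two-sided 0.05, at 60 per arm has power 0.952 for 30% against 5%. A split of 6/60 against 0/60 gives p = 0.027, and 6/36 against 0/36 gives p = 0.025. The first is a total of 6 of 120 participants, or 5%, where the stated rule needs 61. With 30 per arm, power for 30% against 5% is 0.63 (one-sided 0.025). These p-values show sensitivity only and are not proposed triggers.

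**The case against.** The best defence is that the rule is an outer limit. It says when the trial has to stop and does not forbid stopping sooner. SAEs go at once to the principal investigator and by expedited report to the ethics committee, individuals can be withdrawn on safety grounds, emergency unblinding exists, and a monitoring committee has access to unblinded data. All of this stands, and it is why the fault lies in the threshold and its pooling and does not amount to an absence of protection.

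A committee charter, not shown, may hold a by-arm trigger. That also stands: reliance on discretion alone can be asserted only for what the article shows. The article would still carry a badly set mandatory figure.

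The denominator is undefined, and the count of 61 assumes the planned 120. If a running count is checked from the very first participant, the chance of meeting the rule rises to about 72%, 46% and 21% for 80%, 60% and 30% against 5% (20,000 simulated trials). Many of these are chance trips such as 1 of 1. They show that the rule is unstable early, not that it detects harm.

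The 95% power belongs to one test at full enrolment. Earlier power is lower, 0.63 at 30 per arm, before any allowance for repeated looks. That is fair, but at 60 participants the stated rule has a chance of about 6e-11 in the same setting.

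Finally, the remedy replaces a mandatory stop with a review prompt, which is still judgement. This is partly true. The gain is that the judgement would be exercised at set times, on by-arm data, by an independent body.

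**Conclusion.** The concern holds. On the final count, the stop cannot be met even when every YQYYHX participant and no placebo participant has an SAE; this needs only equal arms of 60. For less extreme excesses the result depends on assumed SAE risks, but the conclusion is the same across placebo risks of 2% to 10%: the YQYYHX risk must be roughly 91% to 99% for an even chance of meeting the rule. A running count does not rescue it. A 30% against 5% excess meets it in about 0.4% of trials when checked from the tenth participant, and earlier trips are mostly small-number accidents.

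The flaw does not touch the treatment estimate, the type I error or the primary conclusion. It concerns participant safety and should be fixed while recruitment is open.

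**What to change.** Remove the pooled more-than-half condition. In its place, state that the independent Data Monitoring Committee reviews SAEs and clinically significant liver, renal and ECG abnormalities, unblinded by arm, at the interim look and at regular intervals until the last participant finishes. The trigger should rest on the comparison between arms, with the denominator defined per arm, and be set by the committee with clinical judgement. If its charter already contains such a trigger, the section on suspension and termination should refer to it instead of giving the 50% figure.

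The cost is a protocol or charter amendment and a short unblinded safety table at each review. Investigators stay blind, because only the committee sees that table, and the sample size and efficacy analysis are unchanged. A more sensitive trigger can raise a false alarm on few events, so it should prompt a committee review and not stop the trial automatically.
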